### Procedure

Our recruitment strategy will include (i) drawing on established school networks (e.g., the Schools in Mind network, containing over 30,000 schools), (ii) undertaking an extensive targeted social media campaign towards educational professionals in cities of interest; (iii) attending headteacher network meetings to promote the project; (iv) purchasing the Sprint education database, which contains up-to-date contact details on 570,000 teachers and senior staff at UK schools, (v) offering transparent and accessible communication regarding what school participation entails formalised in a Memorandum of Understanding (MOU), and (vi) compensation of £500 per school for administrative support.

Schools will be recruited by the methods specified above, beginning 01/03/24 and ending 30/06/24 with the aim of starting the pilot interventions on 03/01/25. Schools that express an interest will be asked to fill out a MOU agreeing to participate. As interest is likely to exceed capacity during the pilot, schools will be held in reserve (in case of drop out) or for participation in the full trial. Following recruitment of schools, YP in relevant year groups will be recruited in two stages. Firstly, schools will send letters to parents/carers of pupils in selected classes, including to those identified as persistently absent. The letter will be sent between 16/09/24-31/10/24 and provide information about the study and allow parents/carers to opt their children out of the study. Secondly, for parents and guardians that do not opt out their YP, the YP must assent by reading through an online information sheet and completing an online consent form before they can take part in the baseline survey. Data collection for baseline surveys and YP assent will start on 12/11/24 and be completed by 30/11/24 in all schools. Thus, participant recruitment will be completed by 30/11/24. Follow up data collection will be completed by 01/07/25 and the study completion date is the 31/08/25. For the qualitative interviews, separate information sheets and opt-in consent forms will be provided to parents/carers and YP who are interested in participating.

To identify eligible YP, baseline surveys will be administered to classes of pupils in relevant year groups during PSHE (or another appropriate lesson determined by the school). For pupils who are persistently absent from school, baseline surveys can be completed in their own time (e.g. at home), or with researchers or school pastoral staff at pupils’ convenience. Those who meet the inclusion criteria will then be randomly allocated to receive SP (the intervention) or signposting (the active control). Random allocation will be undertaken by a statistician at the pupil level, stratifying for location. Given the nature of the intervention blinding of participants or researchers is not possible. As LWs will only be able to work with individuals allocated to the intervention arm, this will prevent contamination effects, and all pupils will have access to the same list of community resources. Those allocated to SP will then be contacted by a LW who will arrange a time to meet with them. For those allocated to signposting, researchers will share the names of YP with school pastoral staff who will signpost them to community resources. Any YP identified as having significant mental health issues on the Me & My Feelings questionnaire [34] will be highlighted to pastoral staff regardless of intervention group.

YP who receive SP or signposting will then be followed up at 3 and 6 months using the same measures in the baseline survey, with additional questions on what they thought of the intervention. Participants will receive a £10 voucher for completing follow up measures. Those who were allocated to receive SP or signposting but chose not to receive it will still be given the option of completing follow-up questionnaires for Intention-To-Treat analysis. Feasibility, acceptability, and suitability measures will be administered to school staff and LWs 6 months after the intervention begins. Qualitative interviews with YP will take place at least 3 months after they have received SP and interviews with school staff and LWs will take place at least 6 months after SP has been implemented in their school. Stakeholders will be approached by the research team, taking into account socio-demographic information, questionnaire scores and SP engagement to allow for purposeful sampling. All personal data will be kept on the UCL Data Safe Haven and will be stored securely under a unique numerical identifier. The UCL Data Safe Haven is a certified data transfer and storage system that meets the ISO27001 information security standard and conforms to NHS Digital’s Information Governance Toolkit.

All data collection will be completed by 31/07/25 and results are expected in September 2025.

### Intervention and control

SP is a person-centred approach to wellbeing involving the co-development of a non-clinical prescription, between an individual (in this case, YP) and LW, based on the perceived reasons for the referral and the YP’s values, needs and preferences [24]^.^ LWs have an excellent knowledge of their local areas, via community asset mapping and networking, allowing them to connect individuals with different types of support and activities.

The SP intervention used in this study will be ‘YES’: Youth Engagement in Social prescribing. YES has been developed to connect children and young people with forms of support in their communities to improve wellbeing. It has been used nationally, for example as part of the Wellbeing While Waiting programme which is implementing SP for YP on waiting lists for mental health treatment [35].

The SP intervention will range from 6-12 sessions over an 8-week period. Sessions may take place online, via phone call, or in person. As part of the SP process, LWs will draw on psychological skills such as motivational interviewing and behavioural activation [18] as well as employ problem solving and goal setting [36]. Following the identification of individual needs and preferences, the LW will discuss available local activities and informal sources of support with YP that best match their interests and could help them to feel more connected. Then, with the YP’s agreement, the LW will facilitate their engagement with these activities, which could be done via the LW making links with the organisation and/or accompanying the YP to the first session. All LWs will have undergone training [37] and receive supervision from an experienced mental health professional and/or senior LW.

YP in the control group will receive signposting to social and community activities in their local area. This will consist of school pastoral staff providing YP with a leaflet detailing information on the same local sources of support identified by the LW from asset mapping.

### INACT measures and outcomes

A schedule of enrolment, interventions, and assessments is outlined in Fig 1.

**Fig 1 pone.0317823.g001:**
[figure not shown]
INACT Schedule of enrolment, interventions, and assessments.

#### SP implementation measures.

For school staff and LWs, feasibility, acceptability and appropriateness will be assessed with the Feasibility of Implementation Measure, Acceptability of Intervention Measure and Appropriateness of Intervention Measure [38]. Each questionnaire consists of 4 questions, each on a five-point Likert scale ranging from 1 ‘Completely Disagree’ to 5 ‘Completely Agree’. Higher scores indicate greater feasibility, acceptability, and appropriateness.

As the above measures are not validated to be used with YP, acceptability will also be assessed by the proportion of YP who take up SP after being offered it.

#### Study outcome measures.

The proposed primary outcome measure for INACT is the 3 loneliness questions from the Good Childhood Index [32]. Each question is scored on a three-point Likert scale ranging from 1 ‘hardly ever or never’ to 3 ‘often’. Higher total scores indicate higher levels of loneliness. This is assessed at baseline, 3 and 6 months. The primary timepoint is at 3 month follow up.

Secondary measures were chosen with young person and subject expert input. These include:

*For young people*

Peer loneliness – assessed using the Loneliness and Aloneness Scale for Children and Adolescents (LACA) peer subscale [39]. This consists of 12 questions each on a four-point Likert scale ranging from 1 ‘never’ to 4 ‘always’. Higher total scores indicate higher peer loneliness. This is assessed at baseline, 3 and 6 months.Wellbeing – assessed using the Wellbeing Scale from the Kidscreen-52 [40]. This consists of 6 questions each on a five-point Likert scale ranging from 1 ‘not at all/never’ to 5 ‘extremely/always’. Higher total scores indicate greater well-being. This is assessed at baseline, 3 and 6 months.Emotional difficulties – assessed using the emotional difficulties subscale from the Me and My Feelings questionnaire [34]. This consists of 10 questions each on a three-point Likert scale ranging from 0 ‘never’ to 2 ‘always’. Higher total scores indicate greater emotional difficulties. This is assessed at baseline, 3 and 6 months.Service use – assessed using the Client Service Receipt of Inventory [41]. It consists of 11 questions asking about service use. Of these, 9 questions are about different types of service use and each are answered using a five-point Likert scale ranging between 1 ‘not at all’ to 5 ‘several times a week’. Each item is individually scored, and higher scores indicate more engagement with services. Two further questions ask about pupils accessing school wellbeing support and if they have missed school because of mental health/wellbeing difficulties. This is assessed at baseline, 3 and 6 months.Social Support – assessed using the Child and Youth Resilience Measure [42]. This contains 4 questions each question on a five-point Likert scale ranging from 1 ‘not at all’ to 5 ‘A lot’. Higher scores indicate greater social support. This is assessed at baseline, 3 and 6 months.Social structure and quality using questions adapted from the OECD Programme for International Student Assessment (PISA) 2022 [43] and Millenium Cohort Study 5 [44]. It consists of 5 questions asking about social support and quality. Of these, 4 questions each assess social structure and quality using a five-point Likert Scale ranging from 0 ‘I do not have any friends’ to 4 ‘every day or several times a day/a lot’. Higher scores indicate greater social structure and quality connections. The other question requires a numerical input on how many close friends the YP has. This is assessed at baseline, 3 and 6 months.Bullying – assessed using the bullying subscale from the Kidscreen-52 [40] for primary school pupils and the bullying subscale from the BeeWell survey [45] for secondary school pupils. For the Kidscreen-52 [40] this consists of three questions each on a five-point Likert scale, ranging from 1 ‘never’ to 5 ‘always’. For the BeeWell survey [45] this contains 3 items each on a four-point Likert scale ranging from ‘0” not bullied at all’ to 3 ‘a lot’. In both instances, higher scores indicate higher levels of bullying. This is assessed at baseline, 3 and 6 months.Activity engagement - assessed using the BeeWell survey [45]. It consists of 11 questions on activity engagement each on a six-point Likert scale ranging from 1 ‘never or almost never’ to 6 ‘most days’. Each item can be individually scored, or a higher overall score indicates more frequent engagement in multiple activities. This is assessed at baseline, 3 and 6 months.Local environment – assessed using questions from the Health Behaviour in School-aged Children (HBSC) 2022 survey [46]. It contains 4 questions each on a five-point Likert scale ranging from 1 ‘strongly disagree’ to 5 ‘strongly agree’. Higher scores indicate more positive views of ones environment. This is assessed at baseline, 3 and 6 months.Problem solving – assessed using the problem solving subscale from the Student Resilience Survey [47]. It consists of 3 questions each on a five-point Likert scale ranging from 1 ‘never’ to 5 ‘always’. Higher scores indicate better problem solving. This is assessed at baseline, 3 and 6 months.Family support – assessed using the family support subscale from the Student Resilience Survey [47]. It consists of 4 questions each on a five-point Likert scale ranging from 1 ‘never’ to 5 ‘always’. Higher scores indicate higher family support. This is assessed at baseline only.School support – assessed using the school support subscale from the Student Resilience Survey [47]. It consists of 4 questions each on a five-point Likert scale ranging from 1 ‘never’ to 5 ‘always’. Higher scores indicate higher school support. This is assessed at baseline only.Stress - assessed using the Perceived Stress Scale 4 [48]. This consists of 4 questions each on a five-point Likert scale ranging from 0 ‘never’ to 5 ‘very often’. Higher scores indicate higher levels of stress. This is assessed at baseline, 3 and 6 months. Due to its reading age, this is only being used with secondary school pupils.Flow - assessed using the General Flow Proneness Scale [49]. It consists of 13 items each on a five-point Likert scale each ranging from 1 ‘strongly disagree’ to 5 ‘strongly agree’. Higher scores indicate a higher proneness for flow-state experiences. This is assessed at baseline, 3 and 6 months. Due to its reading age, this is only being used with secondary school pupils.Therapeutic alliance – assessed using the Session Feedback Questionnaire [50]. It consists of four items each on a five-point Likert scale each ranging from 1 ‘not at all’ to 5 ‘totally’. Higher scores indicate higher therapeutic alliance. This is assessed at 3 and 6 months for those in the intervention (SP) group.

### Data analysis

***(Rqi)*** To assess the feasibility, acceptability and suitability of the SP pathway, descriptive statistics will be calculated from stakeholders’ questionnaire data responses, how many YP take up the SP offer, as well as via qualitative interview data which will be analysed using framework analysis [51] a method which allows for both deductive and inductive coding of transcripts across multiple stakeholder accounts.

***(Rqii)*** To assess the feasibility, acceptability and suitability of the study design, descriptive statistics will be calculated exploring measure completion rates, as well as from interview data using framework analysis [51].

Implementation data will be used to determine whether pathway refinements are needed and outcome measures will inform refinements to sample size (establishing ICCs and effect size). Crucially, the project will not proceed to full trial until pre-established “stop-go” criteria have been met (see Table 1). If the criteria are partially met, the research team will further develop trial plans (e.g., tweaking the SP pathway, reducing the number of follow-up measures, etc). This will be signed off by the Trial Steering Committee (TSC) prior to proceeding to full trial.

**Table 1 pone.0317823.t001:** Stop-go criteria.

Method	Indicator	Fully met (proceed)	Partially met (proceed with amendments agreed by TSC)	Not met (stop)
Acceptability of intervention	Qualitative reports of acceptability from young people, school staff and link workers	The majority (>50%) of stakeholders report the social prescribing intervention is acceptable	Some stakeholders report the social prescribing intervention is not acceptable but identify alterations that need to occur	The majority (>50%) of stakeholders report the social prescribing intervention is not acceptable even with modifications
	Proportion of young people attending an appointment with a link worker	55-100%	40-54%	0-39%
Acceptability of evaluation framework	Qualitative reports of acceptability from young people, school staff and link workers	The majority (>50%) of stakeholders report the social prescribing intervention is acceptable	Some stakeholders report the social prescribing intervention is not acceptable but identify alterations that need to occur	The majority (>50%) of stakeholders report the social prescribing intervention is not acceptable even with modifications
	Proportion of young people completing baseline measures	55-100%	40-54%	0-39%
Ability to collect 3-month data from pupils who completed baseline measures	Proportion of young people completing 3 month follow up	55-100%	40-54%	0-39%
Negative consequences of the intervention	Reported negative/adverse effects of social prescribing from young people, school staff or link workers	No evidence of substantially negative effects on young people	–	Evidence of substantially negative effects on young people

***(Rqiii)*** To assess whether power calculation assumptions are realistic, descriptive statistics, and point estimates of the within-person intraclass correlation coefficients (ICCs) for all instruments based on the pilot data will be calculated, as well as a bootstrap study exploring the upper bounds for the ICCs.

Where questionnaire data is missing from participants at random, multiple imputation will be employed. There will be no interim analysis given the short timescale (6 months) that participants are involved in the intervention.

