## Abstract

**Background:**

Social prescribing is a mechanism for connecting patients with non-medical forms of support within the community and has been shown to improve loneliness. Yet uptake from young people (YP) has been lower than for adults. That is thought to be the case because young people are less likely to engage with primary care for wellbeing support, where social prescribing is based. The INACT study will pilot a social prescribing pathway via schools to support young people who are lonely, testing its feasibility and acceptability of delivering, and evaluating its impact on loneliness through a randomised controlled trial.

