SP is supposed to be an ‘all age’ model [24], yet research suggests that uptake from YP remains lower than for adults [25]. While YP see the benefits of SP [26], the dominant model of delivery through family doctors in the UK may be inhibiting youth involvement as they do not feel comfortable accessing wellbeing support in this way [27]. Schools may be better placed to deliver wellbeing initiatives and targeted interventions for loneliness, as they serve as a universal point of access for YP [28]. Schools could act as a conduit to connect YP to community support and have started to be used as a venue to facilitate SP in the UK [29]. The building blocks for SP are already in place, with the rollout of specialist youth LWs across England and an increasing number of community organisations delivering activities suitable for youth SP. However, SP has not yet been properly embedded into schools, and educational stakeholders have been underrepresented in SP pathway development. More work needs to be undertaken to ensure adequate information sharing between agencies, such as schools and LWs [29]. To date, no studies have explored SP in school settings.

Given the high rates of loneliness among YP and the lack of interventions targeting loneliness in this cohort [14], this proposed study will focus on piloting a novel SP pathway in schools for pupils reporting low community connection or loneliness. The aims of this pilot study are to ensure the following:

i)The SP pathway and study design are feasible, acceptable and suitable;ii)The proposed measurement framework is tested for feasibility, acceptability and suitability, andiii)Quantitative data are collected to inform a better estimation of the required sample size for a full trial.

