### Research questions (RQs)

***(RQi)*** Is the SP pathway for youth reporting low community connection or loneliness feasible, acceptable and suitable to stakeholders?

***(RQii)*** Is the study design, including measurement framework, feasible, acceptable and suitable to stakeholders?

***(RQiii)*** Are the assumptions in the power calculation (specifically the intraclass correlation coefficients) realistic to allow for adequate power to be able to test for differences?

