### Participants

We aim to recruit a total of 12 schools (6 primary schools and 6 secondary schools). In each primary school, one class from each of Years 4 and 5 (children aged 9 and 10 years old) will be selected, whilst in secondary schools, two classes each from Years 7 and 8 (children aged 12 and 13 years old) will be selected. Year 6 (children aged 11 years old) will be excluded from taking part because previous studies by the research team have shown that schools are reluctant to engage Year 6 students in research due to exam preparation [30,31]. Private schools will be excluded because they have greater resource to support YP with wellbeing difficulties and do not use unique pupil numbers linked to the National Pupil Database, which will be needed to explore factors associated with low community connection and loneliness.

Approximately 780 pupils (exact number dependant on class size) will complete baseline surveys to examine the prevalence rates of low community connection and loneliness and factors that predict this. Under realistic assumptions from other trials [31] and reviews on low community connection and loneliness [14] (low community connection/loneliness prevalence =  14%, participation rate =  71%), approximately 78 pupils will participate in the pilot study (39 receiving SP and 39 receiving signposting). YP eligible for the pilot study will be those reporting feelings of loneliness (≥6) using the 3 loneliness questions from the Good Childhood Index [32]. This corresponds to YP who report feeling lonely at least some of the time across all three questions. YP who are persistently absent from school will be included. YP reporting severe learning disability will be excluded.

In addition to YP, approximately 20 other stakeholders, namely LWs and school pastoral staff, will participate in the pilot study. Pre-intervention, a single member of staff in each participating school will be asked to complete a school wellbeing provision survey. Typically, this will be the named mental health lead; in schools where there is no named mental health lead, it may be the member of staff with primary responsibility for personal, social and health education (PSHE) provision or pastoral support. Post-intervention, school staff who were involved in signposting and LWs who provided SP will be asked to complete a feasibility, acceptability and suitability survey.

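### The pilot is to supply an effect size for the full-trial sample size, but about 39 pupils per arm cannot estimate one precisely enough for that use

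*Protocol article*

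**What the plan says.** The Data analysis section, after the paragraph on research question ii, states that "outcome measures will inform refinements to sample size (establishing ICCs and effect size". The third aim in the Introduction is that "Quantitative data are collected to inform a better estimation of the required sample size for a full trial"; it does not name the effect size. Research question iii is narrower: "Are the assumptions in the power calculation (specifically the intraclass correlation coefficients) realistic". The analysis given for that question consists of descriptive statistics, point estimates of within-person ICCs, and a bootstrap for the upper bounds of the ICCs. No interval or other allowance for uncertainty is mentioned for the effect size.

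On numbers, the Participants section says that "approximately 78 pupils will participate in the pilot study (39 receiving SP and 39 receiving signposting". The primary outcome is the three-item loneliness score, with 3 months as the primary timepoint. Table 1 rates 55% to 100% completion at 3 months as fully met. All its criteria concern acceptability, attendance, completion and negative effects. The abstract's Background nevertheless describes the pilot as "evaluating its impact on loneliness through a randomised controlled trial", while its Discussion promises preliminary evidence on feasibility and acceptability.

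**The concern.** The required sample size varies as one over the square of the effect size, so error in the effect estimate is magnified when it is carried into a sample size. A pilot of this size estimates a between-group difference poorly. A chance high estimate would point to a full trial that is too small, and a chance low one to a trial that is far too large. The article plans to examine uncertainty for the ICCs but mentions none for the effect size, to which the sample size is very sensitive. At stake is whether the third aim, a better sample-size estimate, is met: refining a sound prior assumption with so noisy an estimate can make it worse.

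**Working it through.** **1. The plan's own figure.** From the Participants section: about 780 pupils surveyed, 14% prevalence, 71% participation.

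780 × 0.14 × 0.71 = 77.5, which agrees with the stated 78, or 39 per arm. This is a recruitment yield; no precision target for an effect is given.

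**2. Pupils with primary-timepoint data.** At the lower edge of the fully met band in Table 1: 39 × 0.55 = 21.45, so 21 to 22 per arm.

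**3. Precision of the standardised difference.** Near zero effect, half-width = 1.96 × √(2/n).

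- n = 39: 1.96 × √(2/39) = 0.44
- n = 21.5: 1.96 × √(2/21.5) = 0.60

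For a non-zero effect, SE = √(2/n + d²/(4n)). At 39 per arm:

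- observed 0.3: SE 0.228, 95% CI −0.15 to 0.75
- observed 0.5: SE 0.230, 95% CI 0.05 to 0.95

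At 21 per arm, an observed 0.5 has a 95% CI of −0.11 to 1.11. Baseline adjustment with an assumed correlation of 0.5 multiplies the half-width by √(1 − 0.25), so 0.44 becomes 0.38.

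**4. What this does to a sample size, under a hypothetical rule.** Assumptions that are not in the article: the observed effect is put directly into the formula; two-sided 5% level; 90% power; individual randomisation without clustering; true effect 0.3 SD; 39 per arm analysed; estimates of 0.05 or less set aside.

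Planned n per arm = 2 × (1.96 + 1.2816)² / d² = 21.02 / d².

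- At the true effect: 21.02 / 0.09 = 233.5, so 234 per arm.
- Share of pilots with an estimate above 0.05: 1 − Φ((0.05 − 0.3)/0.228) = about 86%.
- Among these, the upper 10% point of the estimate is about 0.61: 21.02 / 0.61² = about 56 per arm.
- The lower 10% point is about 0.126: 21.02 / 0.126² = about 1,320 per arm (1,314 by simulation).

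The central 80% of planned sizes therefore runs from about one quarter of the need (56/234 = 0.24) to more than five times it (1,314/234 = 5.6).

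**5. Sensitivity to the assumed target.** Required n per arm at 80% / 90% power:

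| Target effect (SD) | 80% | 90% |
|---|---|---|
| 0.2 | 393 | 526 |
| 0.3 | 175 | 234 |
| 0.5 | 63 | 85 |

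The article calls the effect of earlier youth interventions moderate and gives no number, so these targets are illustrative.

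**6. What the pilot can estimate.** With 76 degrees of freedom, the 95% CI for the pooled SD runs from √(76/χ²₀.₉₇₅) = 0.86 to √(76/χ²₀.₀₂₅) = 1.19 times its estimate, where each subscript is the cumulative probability. That is a usable input, unlike the effect size.

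**The case against.** The strongest reply is that the article does not say that the pilot effect will become the full trial's target difference. It speaks of informing refinements, and research question iii refers to a power calculation that already exists but is not shown. A target difference may already be fixed there. The analysis set out for that question concerns ICCs, and the plug-in rule in the working is not the plan's rule. All of this stands, and it limits the point to the stated use of the effect size.

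Four stronger readings are tempting and not supported:

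- *The full trial will be sized on the pilot effect.* The text says only that outcomes will inform refinements.
- *An underpowered full trial is likely.* This depends on the assumed rule. At 39 per arm with a 90% power target, true power falls below 80% in 48% (true effect 0.3) or 38% (true effect 0.5) of pilots with an estimate above 0.05. With an 80% target and no selection on the estimate, it is about half. Oversizing is a comparable risk.
- *A low estimate could stop the full trial.* Table 1 has no efficacy threshold, so no stated rule would do this.
- *Sample size is the pilot's main output.* It is the third of three aims; the first two concern feasibility, acceptability and suitability.

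The abstract's phrase on impact is one background sentence, and the abstract's Methods say that outcomes are collected to assess response and completeness. It is therefore supporting evidence only.

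None of this removes the sentence in the Data analysis section. It names effect size as something the pilot will establish for sample-size purposes, which these numbers do not allow.

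**Conclusion.** The point holds as a specific defect in a stated intention. An interval of ±0.44 SD with complete data, or about ±0.60 SD at the lowest completion rated fully met, cannot establish an effect size for planning. These half-widths need only the planned numbers and the 55% threshold, and assume independent pupils; clustering by school or link worker would probably widen them. The range of 56 to 1,314 per arm illustrates what direct use of the estimate could do, in either direction. It rests on the assumed level, power, true effect and plug-in rule, and does not predict what the investigators will do. The article is also not consistent with itself: the Data analysis sentence adds effect size to a check that research question iii and its analysis direct at the ICCs. The pilot's own feasibility findings are unaffected; the risk falls on the design of the next trial.

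**What to change.** 1. In the Data analysis section, remove effect size from the sample-size inputs, so that the sentence matches research question iii.
2. State that the full trial's target difference will rest on a pre-specified important difference on the loneliness score or on external evidence. If the existing power calculation already fixes one, cite it.
3. List what the pilot will supply: SD, ICCs and correlations, uptake and retention.
4. Report the pilot's between-group difference with its 95% CI, labelled as descriptive.
5. Reword the abstract's Background sentence on impact to agree with the feasibility aims.

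No data collection changes. The cost is the wording, plus agreeing a target difference in advance if none exists. The Trial Steering Committee and the youth advisers could be asked, but the article describes no meeting for this; it ties the committee's sign-off to partially met criteria, so the step would have to be added.
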